## Description of protocol deviation for the trial

In the end, some schools did require active parental consent for youth to participate in this trial; therefore, not all HR youth were recruited and were provided with interventions in the intervention condition. However, these schools will remain in the study, and considered “compliant”. Only schools that agreed and were able to facilitate follow-up every year were included in the study, regardless of follow-up rate (therefore, compliant). Schools that did not agree to continue to facilitate follow-up of students were considered dropout (non-compliant) and will not be included in the intent to treat analysis. Protocol deviation are defined as departure from the procedures outlined in the protocol. We used a modified intention to treat (ITT) design including only schools that were randomized and followed during 5 years. At the individual level, ITT will be all high-risk students in the schools who consented to a trial and eligible to receive intervention (Regardless of whether or not they received it).

Protocol deviation (PD) was classified prior to unblinding of intervention groups.

1. During the recruitment phase, five schools were recruited and dropped out after the randomisation. Among those, three schools never launched screening and baseline survey, and so were not included. One school dropped out after screening and one school did deliver intervention, but failed to comply with follow-up procedures, so was also dropped from the trial and not included in ITT.
2. Truancy is self-reported and academic records were not obtained.
3. The CMS had to be modified to address ceiling effects in later years of follow-up (one additional item was added in year 3, 4 and 5).
4. School and participant recruitment was completed outside of the planned window since there were two waves of recruitment, students were recruited in the 7th grade in 2012 and 2013.
5. Some procedures not performed. We changed intervention adherence criteria: Overall 86% of HR students received intervention, but some schools had poor implementation which fell below our initial criteria for evaluation. We will control for adherence, rather than require a certain level of implementation. One school closed, but the school remained in the study, because they provided access to student information so that they could be followed individually. One school missed a follow-up survey in year 4 (due to natural disaster, flood) and instead completed two surveys 7 months apart in the final year: they are considered compliant and in the ITT.
6. **Deviation from planned statistical analyses:** when analysing this dataset, it became apparent that the Proc GLIMMIX method in SAS that is described in the analysis plan was not the most appropriate method to analyse this dataset, as this method required that an imputed dataset be generated in order to include all available data in the analysis. Due to the complex structure of this dataset, and the fact that data were missing at the individual and school level, multiple imputation as a method to manage missing data failed to converge, due to the fact that these models have difficulty managing high-dimensional models with correlated parameters. They either take very long to converge, or don't converge at all, especially for dichotomous outcomes. Very recently, the benefits of the Bayesian framework for managing multi-level data with missingness have been highlighted as potential solutions for social and health sciences. A number of solutions now exist using the STAN package in R. The MLM in Bayesian framework is especially useful when dealing with repeated measurements (e.g., when measurements are nested within participants) or when handling complex dependency structures in the data such as unequal sample sizes

or missing data. Many statistical packages are developed to fit MLMs but their functionality is limited to the mean of the response distribution, with other parameters of the response distribution, such as the residual standard deviation in linear models, assumed constant across observations. However, when sample sizes or variances change over time, or when missing data occur at different levels in the structure of a dataset, a maximal varying effect structure is needed and many approaches will give aberrant estimations of the correlation between varying effects. While the Proc GLIMMIX provides estimators to correct for this instability, it is generally agreed that Bayesian approaches are better suited to solve this type of problem, especially for dichotomous outcomes with sparse distribution (few non-zeros). It is also preferred to not have to impute datasets in order to replace missing data, which the Bayesian approach allows. Therefore, a slight deviation from the original analysis strategy involved moving from a frequentist to a BayesianMLM model. STAN uses the brms package and supports diverse distributions and link functions, allowing for multiple grouping factors each with multiple group-level effects. It also allows for autocorrelation of the response variable, user defined covariance structures, an flexibleand explicit prior specifications.

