## **2. The Proposed Trial**

### *2.1 What is the proposed trial design? E.g. Open-label, double or single blinded, etc.*

The study will use a cluster-randomised controlled design to test the effects of personality-targeted interventions on substance use and cognitive outcomes. Thirty-two schools (cluster) will agree to conduct annual surveys for 5 years with all consenting adolescents who are enrolled in Grade 7 in September 2012. Schools will be randomly assigned to 1) be trained to deliver the intervention programme and assisted in delivering the selective programme to this Grade 7 cohort or 2) assigned to receive training at the end of the trial, so that their corresponding Grade 7 cohort is never exposed to the intervention. Intervention schools will be assisted by research staff in organisation, delivery and evaluation of interventions delivered to their high risk students meeting criteria for personality risk. All schools will be assisted by our research team in arranging and implementing baseline and follow-up assessments at 12, 24, 36 and 48 months post-randomisation (Appendix B-Consort Figure).

This selective intervention involves screening all students in the first term of their Grade 7 year on personality dimensions linked to risk for substance misuse. Those scoring one standard deviation above the school mean on one of the following four dimensions will be invited to participate in coping skills workshops: Anxiety sensitivity, Hopelessness, Impulsivity, Sensation seeking. Due to the confidential nature of the selection criteria, this information will only be revealed to the teachers who deliver the training workshops. Feedback will not be provided to high risk youth or their parents.

This trial does not include a placebo condition, nor do we attempt to control for therapist contact in the control condition to avoid possible iatrogenic effects of an untested placebo intervention, which have been observed with youth interventions [90]. Furthermore, several systematic reviews of school-based interventions do not show natural reductions in youth substance use resulting from inactive group sessions.

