## *2.3 What are the proposed practical arrangements for allocating participants to trial groups?*

Randomisation of schools to intervention or control conditions will be on a 1:1 ratio using a restricted randomisation scheme, to match schools on various demographic characteristics linked to substance use. A staggered approach to randomisation, occurring following recruitment of every 10 schools will allow the clinical staff to stagger training and supervision over the course of the first year of the study. [name] and the staff at the Unité de recherche Clinique appliquée (URCA), Ste Justine, will oversee randomisation and will make sure that schools randomised to intervention and control will be matched on SES (private vs. public), size (number of grade seven classes), gender-specificity (mixed, girls-only, boys-only), and language (French vs. English). All students in grades 7 will be invited to take part in the trial, both survey and intervention phases and regardless of risk status. Responses on Substance Use Risk Profile Scale [93] will determine personality risk status (comparisons are made relative to school mean for each personality dimension). All HR students in intervention schools who consent to intervention phase of the study will be invited to take part in interventions delivered by trained school staff. All students, regardless of risk status, will be followed annually until Grade 11.

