## 9. Randomisation

A dynamic allocation (DA) method will be used to allocate schools to intervention or control arms to balance baseline prognostic factors at the cluster (school) level. The Data Coordinating Centre statistician at Hôpital Sainte-Justine ([name], PI) generates randomization lists for school. The randomization process consists of computer-generated random lists of intervention allocations to school according to the Pocock–Simon modified minimization method to ensure balance across two covariates, the language of school (French, English) and the gender with three categories describing the proportion of boys in the school (< 25% boys, 25-75% boys, ≥ 75% boys). Details of the randomisation method are held securely at the Data Coordinating center (ACRU).

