### **26.b Adjustments for primary and secondary outcomes**

To take into account the baseline prognostic factors at the cluster (school) level used for DA (c.f. Section Randomisation), all the results will be adjusted for language of the school, and the gender with three categories.

In case of imbalance for a variable at baseline, interaction and confounding effects will be tested according to its clinical significance.

Modification to protocol: Considering that immigration status has a very large protective effect on youth substance use (including in this sample), and that schools in Montreal vary significantly on this variable, we have modified the analysis plan to also include immigration status (immigrant, first generation, second generation) as a covariate.

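### Schools entered in two Grade 7 cohorts, 2012 and 2013, but entry cohort is not explicitly balanced, adjusted for or tabulated; the likely effect is small and the remedy cheap.

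*Combined protocol and SAP*

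**What the plan says.** - **Planned intake.** Protocol 2.1 enrols "all consenting adolescents who are enrolled in Grade 7 in September 2012", which is one cohort.
- **Actual intake.** The SAP's closing section on protocol deviations states that "there were two waves of recruitment, students were recruited in the 7th grade in 2012 and 2013". SAP 18.d, item 3, says the same. Both present it as activity outside the planned window and attach no consequence for the analysis.
- **Allocation.** Protocol 2.3 describes "A staggered approach to randomisation, occurring following recruitment of every 10 schools", at a 1:1 ratio. SAP 9 describes a Pocock-Simon "modified minimization method to ensure balance across two covariates, the language of school (French, English) and the gender with three categories". Neither names entry year.
- **Adjustment.** Under the SAP heading on adjustments (26.b), "all the results will be adjusted for language of the school, and the gender with three categories". A later modification extends the plan to "include immigration status (immigrant, first generation, second generation) as a covariate". Entry year is not listed.
- **Conditional routes.** The same section adds: "In case of imbalance for a variable at baseline, interaction and confounding effects will be tested according to its clinical significance". SAP 24.b also permits, without requiring, adjusted sensitivity analyses when a relevant variable is substantially unbalanced. The baseline characteristics it lists are demographics and outcomes.
- **Printed models.** Both brms models at the end of the SAP contain DEM_01, arm, language, time, time by arm, and random intercepts for student and school. No cohort term appears. Neither DEM_01 nor the year variable is defined. The heading above the linear model describes growth over time, so year is read here as assessment year.

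**The concern.** Entry cohort is fixed when a school joins. Outcomes are assessed at the same grades in both cohorts (SAP Appendix 3), so the 2013 entrants are assessed about one calendar year later throughout. If substance use differs between the cohorts, that difference sits in the between-school variance. If the arms also differ in their cohort mix, part of it moves into the estimated intervention effect.

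The second cohort was known well before SAP version 1.1 (April 2021). That version added immigration status because it predicts substance use and varies between schools. Entry year is another school attribute already on file, yet it was not considered in the same way. Because it is not among the planned baseline characteristics, a reader of the planned tables could not see whether the arms were balanced on it.

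**Working it through.** **Inputs from the documents.** 31 schools (SAP 20); 15 intervention schools (SAP Table 2), hence 31 - 15 = 16 control; five schools lost after randomisation (SAP 18.d), hence 31 + 5 = 36 taken as randomised. From SAP 10: rates of 10% and 5%, k = 0.35, 50 high-risk students per school, 80% power, 2.5% false positive rate, 15 schools per arm.

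**Not in the documents, so assumed.** The number of schools per cohort and per arm, and any cohort difference in substance use disorder.

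**1. The plan's sample size.**

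c = 1 + (z_alpha + z_beta)^2 x [p0(1-p0)/m + p1(1-p1)/m + k^2(p0^2 + p1^2)] / (p0-p1)^2

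= 1 + (1.96 + 0.84)^2 x [0.0018 + 0.00095 + 0.00153] / 0.0025 = 14.44, rounded up to 15.

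This reproduces the plan's figure with 2.5% read as one-sided. Power at 15 per arm is 81.6%.

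**2. Planned effect on the log odds scale.** ln[(0.05/0.95)/(0.10/0.90)] = -0.75.

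**3. Shift from an imbalance.** Shift = (arm difference in cohort share) x ln(cohort odds ratio). For a 20-point difference:

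| Assumed cohort OR | Shift in log OR | Share of 0.75 |
|---|---|---|
| 1.10 | 0.2 x 0.095 = 0.02 | 3% |
| 1.25 | 0.2 x 0.223 = 0.045 | 6% |
| 1.50 | 0.2 x 0.405 = 0.08 | 11% |

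On the risk scale, assumed cohort differences of 1 to 3 points give shifts of 0.2 to 0.6 points, or 4% to 12% of the 5-point target.

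**4. How likely is a 20-point imbalance?**

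- *Unrestricted allocation, even split of cohorts.* SD of the difference = sqrt[0.25 x (1/15 + 1/16) x 31/30] = 0.183. By normal approximation, P(|difference| > 0.20) = 27%. Exact hypergeometric values for 6 to 15 second-wave schools are SD 0.14 to 0.18 and P(at least 0.20) 17% to 29%.
- *Sequential minimisation on two factors.* This was simulated with 36 schools allocated in order of entry, 8 to 18 of them in the second wave, five then lost at random, assumed factor frequencies, and a biased-coin probability of 0.7 to 1.0. Result: SD 0.08 to 0.14; P(at least 0.20) about 2% to 15%; P(at least 0.30) 0% to 4%.

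The second model is closer to what the documents describe.

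**5. Precision.** The between-school SD on the logit scale implied by k is about 0.035/0.09 = 0.389, variance 0.151. An evenly split cohort factor with OR 1.25 has variance 0.25 x 0.223^2 = 0.0124, about 8% of that. If cohort variance were additional to k = 0.35, with cohorts evenly split, power at 15 per arm would fall from 81.6% to 81.1%, 79.8% or 77.6% for cohort differences of 1, 2 or 3 points. Adjustment would recover about that much.

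**The case against.** The strongest reply is that this is a preference about covariates with little at stake.

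- **Allocation was restricted.** A reader might infer that cohort balance was left to chance. The documents do not support that: batch randomisation and minimisation both tend to keep the arms close within each wave without naming it. This stands, subject to two limits. SAP 9 does not state that schools were allocated in order of entry, and five schools were lost afterwards.
- **Cohort was not a design factor.** With one intake planned, there was nothing to minimise on. This stands, so the criticism reaches only the 2021 SAP and not the randomisation.
- **The cohort effect is assumed.** SAP 6 says hazardous drinking is increasing among young people worldwide. That is no evidence of a one-year change in positive DEP-ADO screens in Montreal. This also stands, which is why a range is shown.
- **The shift is small against sampling error.** The planned effect at 81.6% power implies a standard error near 0.75/(1.96 + 0.90) = 0.26, so a shift of 0.045 is about 0.17 standard errors. This stands.
- **Sections 24.b and 26.b already allow adjustment for imbalance.** This stands only in part. One route is optional and the other depends on clinical judgement; neither names cohort, and the listed baseline characteristics would not reveal the imbalance.
- **A late covariate is not free.** The closing section says the method changed while the data were being analysed, so another term in the primary model would be another post hoc change. This stands and shapes the fix.

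**Conclusion.** This is a true but minor omission. Two entry cohorts replaced one, and the SAP neither balances, adjusts for nor tabulates entry year.

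A reader might go further and infer a biased comparison or an inflated type I error. The documents do not support that: allocation was randomised, and both the planned and printed models carry a school random intercept, so the average bias is zero. The cost is conditional on the imbalance that actually arose, plus a little precision. A 20-point imbalance would shift the log odds ratio by 0.02 to 0.08 under assumed cohort odds ratios of 1.1 to 1.5, and its probability is about 2% to 15% under simulated minimisation. The figure of about 27% belongs to unrestricted allocation and should not be taken as the main estimate.

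The conclusion rests on year being assessment year and on DEM_01 not coding cohort. The real imbalance is unknown because the split by cohort and arm is not given.

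**What to change.** 1. In the baseline table, show the number of schools and of high-risk students by entry cohort (2012 or 2013) and arm.
2. Add entry cohort as one fixed school-level term to the adjustment list, to the models for the primary, supplementary and secondary outcomes (SAP 26.a to 26.c), and to both printed models.
3. If the primary model has already been run, leave it as it is and report the cohort-adjusted fit as a labelled sensitivity analysis beside it.

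The cost is one extra school-level parameter, with no new data needed, and, if added late, one more documented change to the analysis.

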**The script used to create the primary outcome analysis is as follows:**

```
##### model estimating linear growth over time #####
```

```
model_depado <- brm(Flagged ~ 1 + DEM_01 + Exp_Group + Language + year
+year:Exp_Group + (1|id+schoolnum),
data = cov_5,
family = bernoulli,
warmup = 1000,
iter = 3000,
cores = 4,
chains = 4,
seed = 123)
sum_model_depado<-summary(model_depado)
```

```

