**26. Analysis methods****26.a Primary analysis methods used for the primary outcome**

The primary analyses will be the estimation of the effect of the intervention on substance use disorders in high-risk youth in intervention conditions relative to their control counterparts, at the year 5 follow-up (48 months post-intervention). The odds ratio (OR) will be used as the measure of intervention effect for the binary substance use disorders outcome. To account for within-cluster (school) variance, intervention effects will be examined using hierarchical generalized linear modelling (HGLM; using the SAS program, Proc GLIMMIX) using a Bernoulli distribution for the binary primary outcome. The HGLM model will be two-levels, with students as the first level, and nested within schools (clusters) as the second level of the model.

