**26.b Supplementary analysis methods used for the primary outcome**

Similar to the primary analysis, supplementary analysis will be done on the binary primary outcome (substance use disorders) over all post-intervention time points (12 - 48 months), to estimate the effect of the intervention on substance use disorders in high-risk youth in intervention conditions relative to their control counterparts over the 5-year trial (i.e. growth in substance use disorders). To account for within-cluster (school) variance, intervention effects will be examined using HGLM, and the outcomes will be centered at the 12-month follow-up to allow for comparisons between groups post-intervention. The model will be three-levels, with time points as the first level, nested within students as the second level, nested within schools as the third level of the model. When significant effects are revealed on growth, analyses will be conducted (i.e. HGLM) testing intervention effects on onset of use at specific time points while controlling for cluster, using tests based on the Huber-White sandwich estimate of variance.

Supplementary analysis will also be done on the estimation of the effect of the intervention on the continuous value of the primary outcome measure (DEP-ADO scores) between control and intervention group, at the year 5 follow-up (48 months post-intervention). Effect will be analyzed using a mixed effect linear model to compute adjusted mean difference between arms along with their standard errors. The model will be two-levels, with students as the first level, nested within schools as the second level of the model. If there is a violation of distribution assumption on outcomes, appropriate transformation will be used.

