**26.c Analysis methods used for the secondary outcomes**

Using a similar method, secondary analyses will examine the 12-month intercept and the linear slopes (i.e. growth) from 12 - 48 months post-intervention between intervention and control conditions in alcohol and drug use behaviours. Growth terms will be used to detect prevention effects on growth in substance use behaviours over 4 years.

Similar analyses will be carried out for secondary and exploratory outcomes presented in Appendix 3.

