##### model with categorical time variable #####
```

```
cov_5$year_cat=as.factor(cov_5$year)
```

```
model_depado_cat <- brm(Flagged ~ 1 + DEM_01 + Exp_Group + Language +year_cat +
year_cat:Exp_Group + (1|id+schoolnum),
data = cov_5,
family = bernoulli,
warmup = 1000,
iter = 3000,
cores = 4,
chains = 4,
seed = 123)
sum_model_depado_cat<-summary(model_depado_cat)
```

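### The printed growth-model code shows no centring of time and no restriction to the 12–48 month waves, so its intervention row is not shown to be a post-intervention effect

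*Combined protocol and SAP*

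**What the plan says.** SAP 26.a sets the primary analysis as a two-level model of substance use disorder "at the year 5 follow-up (48 months post-intervention"). It does not mention centring.

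SAP 26.b adds a three-level growth model of the same binary outcome "over all post-intervention time points (12 - 48 months"), in which "the outcomes will be centered at the 12-month follow-up to allow for comparisons between groups post-intervention". SAP 26.c (secondary outcomes) keeps the same reference point: "secondary analyses will examine the 12-month intercept and the linear slopes (i.e. growth) from 12 - 48 months post-intervention". Protocol 2.16 states the 12-month centring for secondary outcome variables.

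The end of the SAP prints R code under the line "The script used to create the primary outcome analysis is as follows". The first model, headed as linear growth over time, begins "model_depado <- brm(Flagged ~ 1 + DEM_01 + Exp_Group + Language + year" and continues with "year:Exp_Group + (1|id+schoolnum"). It is fitted to a data set called `cov_5`, and the output is a plain summary. A second model treats time as categorical. The only operation on `year` in the printed code belongs to that second model: "cov_5$year_cat=as.factor(cov_5$year").

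Item 6 of the list of deviations explains the move from SAS GLIMMIX with multiple imputation to a Bayesian multilevel model. It says nothing about centring or about which waves are used.

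**The concern.** The growth model in 26.b has two features that give its arm term a meaning: only post-intervention waves enter, and time is zero at 12 months. Taken literally, 26.b centres the outcome, which is not possible for a 0/1 variable, so it must mean time. Neither feature appears in the printed code.

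Once a time-by-arm interaction is in the model, the arm main effect is the contrast at the zero of the time variable. If that zero lies at or before baseline, the `Exp_Group` row of the linear model describes the arms before the intervention could act, possibly by extrapolation to a time when nobody was observed. The code is labelled as the primary outcome analysis, so a reader may take that row for the intervention effect. A programme that works as hypothesised could then look null or adverse, and the linear model's summary would have no row for the planned 12-month comparison.

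**Working it through.** **Inputs.** Planned rates of 10% (control) and 5% (intervention) in grade 11 come from SAP section 10. The label year 5 = 48 months comes from SAP 26.a and implies year 1 = baseline and year 2 = 12 months. The model terms come from the printed code. The coding and rows of `cov_5` are not in the documents, so each plausible coding is taken in turn.

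**The plan's own figure.** The plan gives no figure for the intervention term. The rates used here belong to its sample size, which reproduces. Per arm, c = 1 + (1.96 + 0.84)² × [p0(1−p0)/m + p1(1−p1)/m + k²(p0² + p1²)]/(p0 − p1)². With p0 = 0.10, p1 = 0.05, m = 50, k = 0.35, 80% power and 2.5% in one tail, c = 14.44, rounded up to 15 schools, as stated.

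**What the arm row means.** In the linear model, log OR(year) = b(Exp_Group) + b(year:Exp_Group) × year. At year = 0 only b(Exp_Group) remains.

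**Illustration.** Assume no arm difference at baseline, divergence linear on the logit scale and the planned rates at 48 months, ignoring clustering.

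- 48-month log OR = logit(0.05) − logit(0.10) = −0.747, so OR = 0.47.
- Slope = −0.747/4 = −0.187 per year, so OR = 0.83 per year.

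| Coding of `year` | Time at year = 0 | `Exp_Group` log OR | OR |
|---|---|---|---|
| 1–5 or 2–5 (the SAP's labels) | 12 months before baseline | +0.187 | 1.21 |
| 0–4, or 1–4 as years since baseline | baseline | 0 | 1.00 |
| centred at 12 months, or 0–3 over follow-ups | 12 months | −0.187 | 0.83 |
| centred at 48 months | 48 months | −0.747 | 0.47 |

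The interaction is −0.187 in every row of the table.

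**Sensitivity to the assumptions.** Logistic fits to expected counts used an assumed control prevalence of 0.5, 1, 3, 6 and 10% by wave and 600 students per arm, again ignoring clustering. With all five waves:

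- Effect growing over time: OR 1.12 (SE 0.56) at year 0 under 1–5 coding, against 0.80 (SE 0.31) at 12 months.
- OR 0.47 at every follow-up and none at baseline: OR 0.66 (SE 0.61) at year 0, against 0.57 (SE 0.34) at 12 months.

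**Row restriction is a separate step.** In the constant-effect case, dropping the baseline wave moves the slope OR from 0.93 to 0.997 and the 12-month SE from 0.34 to 0.42. Centring changes only which contrast is printed, whereas selecting rows changes the fit.

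**The case against.** The strongest reply is that the printed excerpt starts at model fitting. `Flagged`, `Exp_Group`, `DEM_01` and `year` all arrive ready-made, so `year` may have been centred, and baseline rows removed, when `cov_5` was built. The year 5 label in 26.a is prose and does not define a variable, and SAP Table 1 labels the waves in months. This stands: a reader might infer that the arm row is a baseline or pre-baseline contrast, but the documents do not establish that. They show only that no centring is printed and that the SAP's labels point away from 12 months as zero.

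The categorical model also prints an `Exp_Group` row. If `cov_5` holds only follow-up rows, its reference level is 12 months and that row is the planned contrast. If baseline rows are included, the 12-month contrast is that row plus the 12-month interaction. So it would be wrong to say that the output cannot yield the 12-month comparison.

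Finally, the target of a growth model is the slope. Centring is a reparameterisation that leaves the slope and every fitted contrast unchanged, and the 12-month rule belongs to the supplementary model, not to the 48-month primary analysis. All of this is correct and limits the point. It does not explain why a specification with a stated purpose is absent from both the published code and the list of deviations.

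**Conclusion.** The concern holds in a conditional form. The code presented as the primary outcome analysis shows neither the 12-month centring nor the restriction to 12–48 months that SAP 26.b requires of the growth model, and item 6 does not disclose the change. Under the SAP's own year labels, or under a 0–4 or years-since-baseline coding, the `Exp_Group` row of the linear model is not a post-intervention effect. In the planned-effect illustration it reads OR 1.21 or 1.00 where the 12-month value is 0.83. Those figures rest on no baseline difference, logit-linear divergence and no clustering. Under the assumed prevalences and 1–5 coding, the row ranges from 0.66 to 1.12 according to the shape of the effect, so an adverse-looking row is possible but not inevitable.

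A reader might infer that the growth analysis is invalid or that the primary result is wrong. The documents do not support either: the slope is unaffected by centring, and the 12- and 48-month contrasts can be recovered from the fit. What is missing is the definition of `year` and of the rows used, and a printed contrast at the planned times. This should be put right before the arm row is interpreted.

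**What to change.** 1. In SAP 26.b, say that time, not the outcome, will be centred at the 12-month follow-up.
2. In the code, state how `year` is coded and which waves `cov_5` contains.
3. Define `time12` as `year` minus the value coded for the 12-month wave, and use it in both the main effect and the interaction. Subtracting 2 is right only if `year` is coded 1–5 or 2–5; under 0–4, or 1–4 for the follow-ups, it would centre at 24 months.
4. Fit the 12–48 month rows as 26.b states, or record the inclusion of baseline as a deviation, since it can change the slope and its precision.
5. Report `Exp_Group` from that fit as the 12-month odds ratio, and print the 48-month arm contrast as the primary result that 26.a requires. Centring at 12 months does not supply it. With annual coding it is b(Exp_Group) + 3 × b(time12:Exp_Group), because 48 months is three years after 12 months.
6. Do not interpret the `Exp_Group` row of the uncentred linear fit as an intervention effect.

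The cost is one line of code for the centring, a row filter if baseline is present, the printed contrasts, a re-run and a wording correction. No new data are needed.
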